### **D.9. Intervention**

The PREDIMED dietitians are directly responsible for the dietary intervention. All PREDIMED dietitians are registered dietitians, trained and certified to deliver the PREDIMED intervention protocol. Before the implementation of the protocol, training consisted of approximately 24 hours of initial theoretical and practical group discussion with experts in nutrition education and discussion in between 3 to 5 conference calls to review and improve the protocol. These calls are continued bimonthly throughout the study. During the calls each dietitian discusses her practice sessions with the team, and together the group identifies problems and solutions in protocol implementation. Feedback and discussion also occur among the dietitians and the center coordinators, and between center coordinators and the Data Manager, especially after data from FFQ and objective biochemical measurements (in a random sample of 10% participants) of compliance are analyzed.

#### **D.9.1. Delivery of intervention to the 3 groups**

**D.9.1.1. Individual motivational interview** with a PREDIMED dietitian. After screening visit 2, participants randomized to each one of the 3 treatment arms have a face-to-face interview with the dietitian. This interview includes:

**d)** The 14-item questionnaire of adherence to the MeDiet.

**e)** Personal individual recommendations for changes to be introduced in the participant's diet in order to achieve a personalized goal. Depending on treatment group, the dietitian provides a comprehensive number of reasons to either adopt a MeDiet or a low-fat diet, highlighting the advantages of the particular diet, rather than the risks of not adhering to it, and transmitting a positive message with stress on the particular benefits for diabetic patients and for those at high cardiovascular risk. For total fat intake the recommendations given to participants in the Low-fat diet group are in some way opposite those given to participants in the 2 MeDiet groups. Our previous experience with diabetic patients using this approach for a behavioral intervention to quit smoking in Primary Care has been successful (**Canga, 2000**). We also have experience in using the stages of change model for dietary change (**Lopez-Azpiazu, 2000**). The dietitian personalizes the message by adapting it to the patient's clinical condition, preferences, and beliefs. The training of the PREDIMED dietitians emphasized the holistic approach to lifestyle change in order to tailor the intervention to nutritional assessment and individual needs, and encourage adherence to the prescribed diet. A contracting procedure is used and a negotiated change in diet is the targeted goal, working with the subject to determine what he or she considers an attainable goal. The focus can be shifted from changing portion sizes to changing frequency of intake or to changes in cooking methods. Accomplishments in the previous months, even if minor, are considered as support to provide further empowerment and self-reward. The usefulness and effectiveness of this approach was shown in an even larger randomized trial in the US aimed to reduce fat intake, the Women's Health Initiative Study (**Mossavar-Rahmani, 2004; Patterson, 2003**). Importantly, caution is taken to make sure that participants with diabetes, overweight/obesity, and/or hyperlipidemia may not receive

contradictory dietary advice from other health professionals external to the PREDIMED trial. Because unsaturated fats like those contained in olive oil and nuts are still perceived as fattening by some nutrition experts, it is particularly important for participants in the 2 MeDiet groups to allay the fear of an eventual weight gain that might have both the person who is on a weight-management program and his/her nutritionist. This is done by tactful exposition of recent scientific evidences (**McManus, 2001; Ros, 2003; Sabaté, 2003; Garcia-Lorda, 2003**) and by explaining that body weight did not change after 3 months of MeDiet intervention in the pilot phase of the PREDIMED study.

**f)** Depending on group assignment, a leaflet with written information about the main food components and cooking habits of the MeDiet or the low-fat diet, together with recommendations on the desired frequency of intake of specific foods, is given. Participants assigned to the MeDiet group receive an additional leaflet on health benefits, use, and conservation of olive oil, while those in the MeDiet+Nuts are given a leaflet with similar information regarding nuts, with emphasis on the three nut types used in the trial (see: <http://www.predimed.org>).

**d)** The participant is scheduled for a group session in the next 1-2 weeks. The visit ends with an agreement to participate in the group session.

D.9.2.2. Group sessions. The PREDIMED dietitian runs the sessions. No more than 20 participants may attend. Separated sessions are organized for each intervention group (MeDiet+VOO, MeDiet+Nuts, Low-fat diet). The group session includes:

**a)** An introductory talk by the dietitian to remind the 14-item MeDiet score to participants in the two MeDiet groups and a 9-item score of low-fat foods for those in the Low-fat diet group (see: <http://www.predimed.org>). **b)** Clarification of possible doubts about face-to-face counseling or written material.

**c)** The following written material (see: <http://www.predimed.org>) is given to each participant and discussed with them:

- Description of 4-5 foods typical of the MeDiet or the Low-fat diet and adapted to the season of the year.

- A quantitative 1-week shopping list of food items, according to the season of the year.

- A weekly plan of meals (with detailed menus) adapted to the buying list.

- The cooking recipes for cuisine practices according to the suggested menus.

**d)** The needed amount of either olive oil (15 liters = 1 liter/week for 15 weeks) for the MeDiet+VOO participants, sachets of walnuts, hazelnuts, and almonds (1,350 g walnuts = 15 g/d; 675 g hazelnuts = 7.5 g/d, and 675 g almonds = 7.5 g/d, allotment for 90 days) for those allocated the MeDiet+Nuts, or gifts of canned low-fat foods, books, dispensers, etc, for participants in the Low-fat diet group are provided.

**e)** The contact ends with an agreement to participate in the next visit (in the next 3 months).

In the MeDiet+Nuts group we offer participants three kinds of nuts: walnuts, almonds, and hazelnuts, instead of providing only one type of nut, because we have received funding from the nut industry to provide the three of them. As increasing evidences support that alpha-linolenic in walnuts can offer special advantages in cardiovascular prevention, we are supplying a higher amount of walnuts.

#### D.9.2.3. Follow-up visits and reiteration of individual and group sessions

The individual and group visits are repeated every 3 months with the same contents, except that shopping lists and recipes vary with the season of the year. Each visit includes three steps: assessment, intervention, and future directions.

#### D.10. Description of intervention diets

Our main focus is to change the **dietary pattern** instead of focusing on changes in single foods or macronutrients. Total fat intake for the 2 MeDiet groups is *ad libitum* (a high fat intake is allowed, as long as most fat is derived from fatty fish and vegetable sources, particularly olive oil or nuts), while it is curtailed in the Low-fat diet group. There is also no specific energy restriction. Total energy intake is adapted to participant's weight, age and requirements, and dietitians tailor advice to individual needs.

The guidelines that PREDIMED dietitians provide to participants in the MeDiet groups are based on the 14-point MeDiet score (**Table 4**), and those for participants in the Low-fat Control diet are based on the 9-point low-fat diet score (**Table 5**).

##### D.10.1. Menu development

Most studies that have examined the MeDiet have been conducted under relatively controlled conditions, with most foods provided to a reduced sample of participants by the research team. The PREDIMED trial represents a further step to obtain more relevant information for public health use, because the nutritional intervention is undertaken in free-living persons, who receive information, motivation, support and empowerment to modify their food habits in a real-life context, i.e., they continue to buy their foods and cook their meals. Such an intervention provides a realistic scenario that may be easily applied to public health policies. However, since palatability of meals is extremely important to ensure compliance, menus and recipes with these characteristics for the two intervention diets have been developed. Menus are designed to meet the nutrient targets. They are provided to the participants and they may learn to prepare the menus using the recipes and the information given by dietitians.

##### D.10.2. Food supply and distribution

A 15-liter supply of EVOO rich in polyphenols (Fundación Patrimonio Comunal Olivarero, Spain) is provided every 3 months to each participant in the MeDiet group. Similarly, every 3 months a supply of 1,350 g walnuts (California Walnut Commission, Sacramento, CA), 675 g almonds (Borges SA, Reus, Spain), and 675 g hazelnuts (La Morella Nuts, Reus, Spain) is provided to each participant assigned to the MeDiet+Nuts group. Participants at each site pick up olive oil and nut allowances at the time of the 3-month group visit. Individualized methods of food delivery have been devised for occasions in which participants need to have their 3-month session rescheduled. Provisions have been made to improve participants' compliance in the 2 MeDiet groups. The olive oil allowance (1 liter/week) takes into account the needs of the whole family. Also, additional 1000 g packs of mixed nuts are provided for each family unit every 3 months. The three nut industry companies are committed to supply for free the nuts used in the study until its termination. None of the investigators has any conflict of interest with these food companies.

#### D.10.3. Promotion of adherence

Efforts to promote adherence began at the earliest stages of the study. During screening and orientation, participants are repeatedly provided with information about key features of the study and with the concept of MeDiet and low-fat diet. At the first screening visit, the attitude towards dietary change is assessed in the eligibility questionnaire. Individuals must be willing to change their dietary habits, otherwise they are excluded. The dietitian-led motivational and education intervention includes both individual and group sessions every 3 months, totaling 32 intervention visits during the trial. Additional written material is provided. Furthermore, the free distribution and supply of key food items ensures a high adherence to the intended diets during the trial. Acceptance of the intervention protocol is increased because no specific caloric restriction is imposed and participants in the two MeDiets are allowed *ad libitum* fat intake, if it comes from olive oil, nuts, other plant-sources or fatty fish. However, after randomization, every effort is made to promote adherence. In many instances, these efforts are tailored to the specific needs of the participant (e.g. food items delivered to home or work). These procedures are very effective as evidenced by the high rates of adherence and follow-up in the pilot study.

#### D.10.4. Assessment of compliance

The yearly-administered FFQ will provide information about compliance and attainment by participants of the nutrients targets. Although the FFQ that we are using has been previously validated in Spain (**Martin-Moreno, 1993**), we have performed a sub-study with 150 participants completing 2 FFQ, one at baseline and another at the end of 1 year, together with four 3-day food records separated by 3 months, to validate and calibrate it again. The validity indexes of the FFQ in relation to the food records for food groups and energy and nutrient intake had intra-class correlation coefficients between 0.40 and 0.84. Regarding food groups, between 68 and 83% of individuals were in the same or adjacent quintile using both methods. The FFQ measurements had therefore good reproducibility and a level of validity similar to those of FFQs used in other prospective studies. The validation of the FFQ ensures a better quality in the measurement of actual diets and will allow corrections for measurement errors.

At any rate, the information extracted from the FFQ will only provide a subjective assessment of compliance. To obtain also an objective evaluation, we measure biological markers of compliance in a random subset of participants from the three arms of trial. In a random sample of 10% of participants, a blood sample and urine aliquots are used to blindly ascertain the following markers of compliance: a) plasma fatty acid composition (specially oleic and alpha-linolenic acid, which are reliable indicators of MUFA and walnut consumption, respectively); b) urinary tyrosol and hydroxytyrosol (EVOO); c) urinary resveratrol and ethanol (wine and other alcoholic beverages). To relate these measurements to the time of intake, participants are asked the time spent since they last consumed the specific foods when blood and urine samples are taken.

### D.11. Measurements

Table 1 shows major measurements and data collection activities by visit.

**Table 1. Overview of measurement scheduled in the PREDIMED trial.**

|                                | BASELINE | YEAR-1 | YEAR-2 | YEAR-3 | YEAR-4 | YEAR-5 | YEAR-6 |
|--------------------------------|----------|--------|--------|--------|--------|--------|--------|
| 1. ELIGIBILITY QUESTIONNAIRE   | X        |        |        |        |        |        |        |
| 2. GENERAL QUESTIONNAIRE       | X        |        |        |        |        |        |        |
| 3. FOOD FREQ. QUESTIONNAIRE    | X        | X      | X      | X      | X      | X      | X      |
| 4. PHYS. ACTIV. QUESTIONNAIRE  | X        | X      | X      | X      | X      | X      | X      |
| 5. FOLLOW-UP QUESTIONNAIRE*    |          | X      | X      | X      | X      | X      | X      |
| 6. TOLERANCE QUESTIONNAIRE     |          | X      | X      | X      | X      | X      | X      |
| 7. ABANDONMENT QUESTIONNAIRE** |          | X      | X      | X      | X      | X      | X      |
| 8. EKG                         | X        | X      | X      | X      | X      | X      | X      |
| 9. BLOOD SAMPLE                | X        | X      |        | X      |        | X      | X      |
| 10. URINE SAMPLE               | X        | X      |        | X      |        | X      | X      |
| 11. TOE NAIL SAMPLE            | X        |        |        |        |        |        |        |

\*Includes measurements of weight, height, waist circumference, BP, and ankle-brachial blood pressure index.

\*\*Only if applicable.

#### D.11.1. Questionnaires

Nine questionnaires (#1 to 7 in Table 1) are shown in <http://www.predimed.org>. The PREDIMED dietitians are responsible for the accurate filling of the questionnaires. The follow-up questionnaire (#7 in Table 1) collects information about the following issues:

- Socio-demographic variables (changes since baseline): 7 items.
- Changes in smoking habits: 3 items.
- New medical diagnoses of diabetes, hyperlipidemia or hypertension: 3 items.
- New medical diagnoses of cardiovascular events: 10 items.
- Inquiries about non-cardiovascular complications of diabetes: 3 items.
- Other medical conditions: 3 items.
- Current use of medication (including doses): 20 items.
- Time since the last intake of EVOO.
- Time since the last intake of wine or other alcoholic beverages.

#### D.11.2. Blood pressure (BP) and anthropometric measurements

PREDIMED nurses, who are trained and certified for these measurements, measure BP, body weight and height. Several quality control procedures are used to promote measurement accuracy. For BP measurements, participants rest quietly for five minutes in the seated position. A validated semi-automatic sphygmomanometer (Omron HEM-705CP) is used for the PREDIMED trial. An appropriate sized cuff is applied after measurement of arm circumference. A pulse obliteration pressure is obtained. At each visit, 3 measurements will be obtained, separated by 2 minutes. The average of second and third measurement is written in the data collection form. If both measurements differ more than 5 mmHg, the whole procedure is repeated and additional BP readings are averaged. Weight is measured using a calibrated balance beam scale with the subject barefoot and wearing light clothes. The nurse measures height using a wall-mounted calibrated stadiometer. Waist circumference is measured using an anthropometric measuring tape, at a horizontal plane midway between the lowest rib and the iliac crest.

### D.11.3. Electrocardiograms (EKG)

At each yearly visit, the nurse obtains from the clinical record the last available EKG, and collects 2 copies. If no EKG has been taken during the last year, she communicates with the Primary Care physician to perform a new EKG and 2 copies are included in the PREDIMED file of the participant.

### D.11.4. Extraction, processing and storage of biological samples

The PREDIMED nurses are directly responsible for collection, processing and storage of biological specimens. All PREDIMED nurses are experienced and registered nurses trained and certified to perform the specimen collection protocol. Training, before starting the trial, consisted of approximately 4 hours of theoretical information and 4 hours of practical instruction. Blood samples are collected at baseline and years 1, 3, 5 and 6 (or final visit) of follow-up according to the protocol shown in Table 2.

**Table 2. Blood samples taken at specified intervals.**

|                              | Number of tubes | Volume (ml) |                                             |
|------------------------------|-----------------|-------------|---------------------------------------------|
| Glass tube K3E EDTA          | 4               | 4.5         | EDTA Plasma + buffy coat                    |
| Plastic tube K3E EDTA (cold) | 1               | 3           | Cold EDTA plasma (pre-refrigerated tube)    |
| Glass tube 9NC Citrate       | 1               | 4.5         | Citrate Plasma + buffy coat                 |
| Gel-Glass tube SST           | 2               | 4           | Serum (one of them light-protected for Hcy) |
| Glass tube K3E EDTA*         | 1               | 5           |                                             |
| TOTAL                 | 9        | 38.5 |                                             |

\*Only a random sample (10%) is analyzed for biomarkers of compliance: the remaining is stored for future analyses.

The plastic tube K3E EDTA (cold) and 1 gel-glass tube SST (for homocysteine) are refrigerated in ice prior to blood collection; after blood is collected, the tubes are kept cold in the ice container. Serum, citrate plasma and EDTA plasma samples are distributed in aliquots of 200 and 500 microliters, and stored at -80°C for later analyses in the central laboratory. Biochemical measurements will be performed blindly and in the same batch for consecutive samples of each participant. Every FC has acquired a freezer with enough capacity to store these specimens. A urine sample is taken at the time of blood extraction, and 16 aliquots (650 microliters) are stored at -80°C. Depending on the available funding for the PREDIMED trial, some of the blood samples could be omitted on years 2-4. All biological samples are processed at each FC not later than 2 hours after collection. During transport from the PCC to the FC laboratory, they are stored in a portable cooler (-4°C). A clip of each toenail of each participant is stored at room temperature.

In addition, a complete blood count and routine biochemical measurements are performed yearly in the PCC (fasting blood glucose, uric acid, ALT, AST, gamma-glutamyl transpeptidase, alkaline phosphatases, bilirubin, creatinine, BUN; total, HDL-, and LDL-cholesterol; triglycerides, total protein, and albumin) together with a routine urine exam including the albumin/creatinine ratio in a recent sample. Genomic DNA has been isolated from leukocytes of all participants and some polymorphism in candidate genes that may modulate the cardiovascular response to diet (LIPC, LPL, PPARG, APOE, PON1, MTHFR, and others) are analyzed by PCR and further allelic discrimination. Some members of our team have played a relevant role in identifying gene-diet interactions, which can be of interest in our project (Ordovas, 2001; Corella, 2002).

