**Table 2. Blood samples taken each year.**

|                                     | Number of tubes | Volume (ml) |                                                    |
|-------------------------------------|-----------------|-------------|----------------------------------------------------|
| Glass tube K3E EDTA          | 4        | 4.5  | EDTA Plasma + buffy coat                    |
| Plastic tube K3E EDTA (cold) | 1        | 3    | Cold EDTA plasma (pre-refrigerated tube)    |
| Glass tube 9NC Citrate       | 1        | 4.5  | Citrate Plasma + buffy coat                 |
| Gel-Glass tube SST           | 2        | 4    | Serum (one of them light-protected for Hcy) |
| Glass tube K3E EDTA*         | 1        | 5    |                                                    |
| TOTAL                        | 9        | 38.5 |                                                    |

\*Only a random sample (10%) is analyzed for biomarkers of compliance: the remaining is stored for future analyses.

The plastic tube K3E EDTA (cold) and 1 gel-glass tube SST (for homocysteine) will be refrigerated in ice prior to blood collection; after blood is collected, the tubes will be kept cold in the ice container. Serum, citrate plasma and EDTA plasma samples will be distributed in aliquots of 650 microliters and stored at -80°C for later analyses in the central laboratory. Biochemical measurements will be performed blindly and in the same batch for consecutive samples of each participant. Every FC has acquired a refrigerator with enough capacity to store these specimens. A urine sample will be taken yearly from each participant, and 16 aliquots (500 microliters) will be stored at -80°C. Depending on the available funding for the PREDIMED trial, some of the blood samples could be omitted on years 1-4. All biological samples will be processed at each FC not later than 2 hours after collection. During transport from the PCC to the FC laboratory, they will be stored in a portable cooler (-4°C). A clip of each toenail of each participant is stored at room temperature.

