## **D.3. Outcomes**

- Primary outcome: composite endpoint of cardiovascular death, non-fatal myocardial infarction, and non-fatal stroke.
- Secondary outcomes: death of any cause and incidence of angina leading to a revascularization procedure, heart failure, diabetes mellitus, cancer, dementia, and other degenerative disorders.

- Other outcomes: changes in blood pressure, body weight, adiposity measures, blood sugar, lipid profile, markers of inflammation, and other intermediate markers of cardiovascular risk (see also section D.11.5)

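### Protocol D.11.4 sets the transport of blood not yet separated at -4°C, below its freezing point: probably a sign slip, but the figure and the place of separation need correcting

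*Supplement*

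**What the plan says.** The blood-handling rules are in the text under Table 2 in D.11.4 of Protocol Version 2 (May 2009).

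- Place and time of processing: "All biological samples are processed at each FC not later than 2 hours after collection".
- Transport, in the next sentence: "During transport from the PCC to the FC laboratory, they are stored in a portable cooler (-4°C". No range, tolerance or warning against freezing is given.
- Two tubes, the cold EDTA tube and the serum tube for homocysteine, have their own rule. They are put in ice beforehand, and "after blood is collected, the tubes are kept cold in the ice container".
- Deep freezing is for separated material: "Serum, citrate plasma and EDTA plasma samples are distributed in aliquots of 200 and 500 microliters, and stored at -80°C".

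Version 1 (D.8.4) gives the same transport figure: "they will be stored in a portable cooler (-4°C".

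D.8 reads differently on place. Under screening visit 2, the nurse draws the blood and goes on to prepare the serum, plasma and buffy-coat aliquots. It does not say that tubes travel first.

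The stored material has two main uses. D.3 lists changes in "lipid profile, markers of inflammation, and other intermediate markers of cardiovascular risk" among the other outcomes. D.10.4 uses it to check adherence: "In a random sample of 10% of participants, a blood sample and urine aliquots are used to blindly ascertain the following markers of compliance".

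**The concern.** Read literally, D.11.4 tells staff to carry blood that has not been separated at a temperature below its freezing point. If a tube freezes before it is spun, the cells can break and release their contents into the plasma or serum. Handling each participant's consecutive samples in one assay batch, as D.11.4 requires, controls assay drift but cannot undo damage done before separation.

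The instruction also sits badly with its own paragraph. An ice container is close to 0°C (assumption), yet the transport sentence covers all samples, including the two tubes kept on ice. Each FC works with about 20 PCCs (D.5.1), so sites could reasonably follow either rule.

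At stake are the stored-sample markers that A.2 and D.3 intend to use to explain how diet changes clinical risk, and the plasma fatty-acid check on adherence in D.10.4. Uneven handling would add variation by centre and visit to measured changes.

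**Working it through.** The temperature is a bare setting, so there is no derived figure to reproduce. The check is a reading of the text plus two side calculations on assumed physical values, none of which is in the documents.

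**1. What is carried.** Table 2 lists EDTA, citrate and serum-gel tubes: 4×4.5 + 1×3 + 1×4.5 + 2×4 + 1×5 = 38.5 ml in 4+1+1+2+1 = 9 tubes, which agrees with the printed total. D.11.4 places processing at the FC, so on its text these tubes travel unseparated.

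**2. Freezing point.** Formula: freezing point = -1.86°C × osmolality (osmol/kg). Assumed osmolality: 0.27 to 0.35.

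- 0.27: -1.86 × 0.27 = -0.50°C
- 0.35: -1.86 × 0.35 = -0.65°C

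The stated -4°C is lower by 4 - 0.50 = 3.50°C to 4 - 0.65 = 3.35°C. A freezing point of -4°C would need 4/1.86 = 2.15 osmol/kg.

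**3. Can a tube freeze within 2 hours?** Simple cooling model for one 4.5 ml tube in surroundings at -4°C.

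- Surface A = π × 0.013 × 0.06 = 0.00245 m² (13 mm by 60 mm tube)
- Heat capacity C = 4.5×3.8 + 8×0.8 = 23.5 J/K (blood plus 8 g of tube)
- Freezing point Tf = -0.55°C
- Heat of freezing L = 4.5 × 0.83 × 334 = 1,247 J
- Time to Tf: t = C/(hA) × ln[(T0+4)/(Tf+4)]
- Largest share of L removed by 120 min: hA × (Tf+4) × (7,200 s - t)/L, capped at 1

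Worked line for h = 5 W/m²K and T0 = 22°C: t = 23.5/(5×0.00245) × ln(26/3.45), about 3,875 s or 64.6 min. The share is 5×0.00245×3.45×(7,200 - 3,875)/1,247 = 0.11.

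| h (W/m²K) | Start (°C) | Minutes to freezing point | Largest share of freezing heat removed by 2 h |
|---|---|---|---|
| 5 | 22 | 64.6 | 0.11 |
| 5 | 37 | 79.1 | 0.08 |
| 10 | 22 | 32.3 | 0.36 |
| 10 | 37 | 39.6 | 0.33 |
| 20 | 22 | 16.1 | 0.84 |
| 20 | 37 | 19.8 | 0.81 |
| 50 | 22 | 6.5 | 1.00 |
| 50 | 37 | 7.9 | 1.00 |

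The shares are ceilings. The model ignores supercooling and keeps the tube in the cooler for the full 2 hours, although that limit runs from collection. Freezing is therefore possible across the range but certain nowhere.

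**4. Which results are exposed.**

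- Exposed: markers measured in stored plasma or serum, such as inflammation markers, and plasma fatty acids in the 10% compliance sample (0.10 × 7,350 = 735 participants, using the recruited total in D.5.3).
- Not exposed: the blood count and routine biochemistry, including lipids and glucose, which D.11.4 places in the PCC; blood pressure, weight and adiposity; and the clinical primary endpoint.
- The urinary compliance markers in D.10.4 do not depend on separating cells from plasma.

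**5. Which visits a correction can reach.** D.5.3 has recruitment finished on 31 March 2009, and Version 2 is dated May 2009. Baseline blood had therefore been taken already. What remains is follow-up blood due from then on (years 1, 3, 5 and 6 or final visit), and D.11.4 allows some samples in years 2-4 to be dropped for lack of funds.

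**The case against.** The strongest reply is that this is a one-character slip. The paragraph speaks of a cooler and an ice container and freezes only separated aliquots, so nobody means blood to be frozen before it is spun. That is probably right, and it lowers the weight of the point. It does not make the written rule correct: the same sign stands in both versions, although the sampling text around it was edited between them.

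Second, D.8 can be read as having aliquots made at the visit. If separation came before transport, cell damage of this kind would not arise. This stands as an open ambiguity. D.11.4 is the more explicit statement on place, and the two sections need to agree.

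A reader might infer that the stored biomarkers are spoiled, or that every sample from about 7,350 participants is affected. The documents do not support either reading:

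- They do not give the share of samples carried from a PCC. D.6.2 mentions 3-monthly visits at the FC, so some blood may not have travelled.
- They report no haemolysis.
- The pilot (C.3), run while Version 1 carried the same figure, found differences from control in ICAM-1, VCAM-1 and interleukin-6. That does not show that handling was sound, but it sits poorly with wholesale loss.

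A reader might also infer bias between the diets. The transport rule is the same in all arms, allocation sequences are separate for each FC (D.8), and measurement is blind (D.11.4). Centre artefacts should therefore be roughly balanced.

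Finally, the Manual of Operations is cited but not shown, and it may already hold the right figure. That is a reason to check it before editing the protocol.

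**Conclusion.** The point holds as a small, cheap correction to an operating instruction. D.11.4 states a transport temperature about 3.4°C below the freezing point of blood for samples it describes as not yet processed, and this conflicts with the rest of its own paragraph. Followed literally, it could partly or fully freeze some tubes within the 2-hour window. How many is unknown.

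The expected cost is noise or lost samples in the stored-sample intermediate and compliance markers from the remaining follow-up visits. No bias between arms is expected, provided that handling does not differ by arm. The primary endpoint and the PCC routine tests are not affected.

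The conclusion rests on an assumed osmolality of 0.27 to 0.35 osmol/kg, on assumed heat transfer of 5 to 50 W/m²K, and on D.11.4, not D.8, describing where separation takes place. The documents do not state which temperature was intended.

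**What to change.** 1. Check the transport temperature in the Manual of Operations, then correct the figure in D.11.4 to chilled but unfrozen.
2. Add one sentence to D.11.4 saying that blood must not freeze before plasma and serum are separated.
3. Reconcile D.8 (screening visit 2) with D.11.4 on where aliquots are made, so that it is clear whether tubes or aliquots travel.
4. Optional: a tick-box for visible haemolysis when aliquots are made.

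The cost is a few words in two sections and a check of the manual. D.11.4 already provides for coolers and an ice container, so no new equipment should be needed. The change cannot help baseline samples, which had been collected by the date of Version 2.
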